## Consent of potential participants

Consulting clinicians, or the study PI, will verbally consent patients to allow the study team to access their medical records to determine eligibility into the study. Consent will be recorded either electronically or in hardcopy patient notes. Upon consent, study nurses will review case notes to determine potential inclusion. The treating team can also let the trial nurse know if there is a potential participant under their care. If Hepatic Encephalopathy is the admission criteria or a present as a concurrent condition on admission the investigator needs to provide an assessment for Encephalopathy using a standard assessment – the West Haven Criteria. A score of 0 or 1 documented in the patient notes by the treating team or trial investigator means that the patient can be approached for consent. Participants who meet inclusion criteria and do not have exclusion criteria will be approached by the site investigator or site nurse. Investigators or nurses can obtain consent for the trial. Potential participants will be inpatients in hospital, or approached after an outpatient appointment, and will receive the information sheet with an explanation about the trial by investigators or nurses and be given opportunity to discuss the trial with family members or to consider the trial. Consent will occur before the patient is discharged from the hospital and can be obtained by investigators or trial nurses. Both consent for the ALFIE trial as well as specific consent for access to MBS and PBS data will be sought. The intervention will commence prior to discharge from hospital.

Patients with mild cognitive impairment may be approached and consented for the study at the site PI’s discretion. If required, a third-party person responsible PISCF can be provided by the PI or study coordinator to the person responsible for the potential participant to obtain informed consent.

The patient will be reassured verbally that their medical care in hospital will not be affected by their participation or non-participation in the trial.

*Recruitment during the COVID-19 Pandemic*

Due to the COVID-19 pandemic and the need to maintain social distance from all potential participants, recruitment methods will be altered to ensure patient and staff safety.

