## Outpatient review by Specialist Gastroenterologist/Hepatologist

Review by a specialist must be scheduled within 1 month (4 weeks) of discharge from hospital for all patients in the intervention group. The nurse must attend this appointment with the patient. In preparation for the outpatient appointment the following should be updated:

- - Medication list
  - Care Plan
  - Ensure screening and surveillance requirements are up to date (or booked)

At this appointment the specialist will discuss the care plan with the nurse and the patient and sign off on the care plan.

## Month 3, Month 6, Month 12, Month 18

Patients in the intervention group have their Child Pugh and Meld scores completed at 3, 6, 12, 18 months and at end of trial (Appendix N). Collect the information from the most recent bloods taken as part of usual care, the patient will not be required to have a blood test taken just for this score to be done.

Surveys are due for both groups at this time. For intervention patients this should ideally be scheduled at the same time the specialist outpatient appointment is scheduled to enable accurate determination of the Child Pugh and MELD score. Ensure the contact log is up to date. Patients will be provided the option of receiving the surveys via standard post or electronically, via email, at consent.

Record hospital and liver-related outpatient admissions/attendances/non attendances at the month 12 visit.

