# Outcomes

## Unplanned liver-related hospital admission rate

Unplanned liver-related hospital admission rate will be the primary outcome measure of the trial. Other hospitalization measures, as outlined in the Aims section, will be measured as secondary endpoints.

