## Randomization, stratification, blinding

Following informed consent, randomization (75 patients in each arm) will occur via telephone call to a third party (Flinders Medical Centre Research Department, Adelaide), with subsequent selection of opaque, sealed envelopes containing the treatment arm allocation number. To prevent imbalance in disease aetiology, stratified block randomization will be performed for disease aetiology. Strata for alcohol, hepatitis C and “other causes” will occur. With three strata and block sizes of four, the maximum imbalance between treatment groups at the end of randomization will be six, which will not significantly affect statistical power. Blinding of care providers (trial nurses and gastroenterologists) will not be possible with this trial design but outcome assessors will be blinded.

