## Statistical methods

All analyses will be performed according to an intention-to-treat protocol. Differences between groups for hospitalization rates, quality indicators, satisfaction rates and self-management scores will be assessed using negative binomial regression, which is appropriate for count data with evidence of over-dispersion. All models will allow adjustment for baseline values and other co-variates. Suitable transformations will be applied in the case of non-normally distributed data.

For the economic analysis mean costs between the intervention and control groups will be compared and incremental cost effectiveness ratios presented with confidence intervals. Cost effectiveness acceptability curves for varying threshold values of cost effectiveness will also be presented ([46](#_ENREF_46)). An assessment of the sensitivity of the results obtained to variation in measured resource use, effectiveness and/or unit costs will be undertaken using appropriate one-way and multi-way sensitivity analysis ([47](#_ENREF_47)). Differences between groups in quality of life scores will be assessed using mixed effects regression to account for the repeated measures (every 3 months) and subsequent within-Participant correlation. Survival analysis will be performed using Cox regression with results presented as Kaplan-Meir survival curves.

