**Period of review (tick only one):**

□ Randomisation Date ___ / ___ / ____ to 12 months ___ / ___ / ____

□ 12 months ___ / ___ / ____to trial end ___ / ___ / ____

( NB If currently in hospital this counts as an admission in the time period being considered)

| Admission 1 |
| --- |
| Admission Date ___ / ___ / ____ Medically Stable for D/C Date ___ / ___ / ____  Discharge Date ___ / ___ / ____  Primary reason for admission as per D/C summary: __________________________  Liver Related Yes  No  Was this a decompensation Event? Yes  No  Emergency  or Elective  (Tick only one)  Number of days in ICCU (please state ‘0’ if not in ICCU): _______ |
| Admission 2 |
| Admission Date ___ / ___ / ____ Medically Stable for D/C Date ___ / ___ / ____  Discharge Date ___ / ___ / ____  Primary reason for admission as per D/C summary: __________________________  Liver Related Yes  No  Was this a decompensation Event? Yes  No  Emergency  or Elective  (Tick only one)  Number of days in ICCU (please state ‘0’ if not in ICCU): _______ |
| Admission 3 |
| Admission Date ___ / ___ / ____ Medically Stable for D/C Date ___ / ___ / ____  Discharge Date ___ / ___ / ____  Primary reason for admission as per D/C summary: __________________________  Liver Related Yes  No  Was this a decompensation Event? Yes  No  Emergency  or Elective  (Tick only one)  Number of days in ICCU (please state ‘0’ if not in ICCU): _______ |
| Admission 4 |
| Admission Date ___ / ___ / ____ Medically Stable for D/C Date ___ / ___ / ____  Discharge Date ___ / ___ / ____  Primary reason for admission as per D/C summary: __________________________  Liver Related Yes  No  Was this a decompensation Event? Yes  No  Emergency  or Elective  (Tick only one)  Number of days in ICCU (please state ‘0’ if not in ICCU): _______ |

| Admission 5 |
| --- |
| Admission Date ___ / ___ / ____ Medically Stable for D/C Date ___ / ___ / ____  Discharge Date ___ / ___ / ____  Primary reason for admission as per D/C summary: __________________________  Liver Related Yes  No  Was this a decompensation Event? Yes  No  Emergency  or Elective  (Tick only one)  Number of days in ICCU (please state ‘0’ if not in ICCU): _______ |
| Admission 6 |

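### The primary model cannot adjust for the baseline value of its own outcome, because no form or schedule records admissions before randomisation

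*Protocol*

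**What the plan says.** The primary outcome is fixed in the Outcomes section of the protocol: "Unplanned liver-related hospital admission rate will be the primary outcome measure of the trial". The Statistical methods section assigns hospitalisation rates to "negative binomial regression, which is appropriate for count data with evidence of over-dispersion", and then adds: "All models will allow adjustment for baseline values and other co-variates".

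Data on admissions come from the Hospital Admission Log (Appendix J). It offers two review windows. The first is "Randomisation Date ___ / ___ / ____ to 12 months"; the second runs from 12 months to trial end. The section on Months 3 to 18 gives the first collection point: "Record hospital and liver-related outpatient admissions/attendances/non attendances at the month 12 visit". The second is the end-of-study visit.

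On eligibility, the consent section says: "Upon consent, study nurses will review case notes to determine potential inclusion". Inclusion criterion 3 uses a hospital admission in the previous 6 months as a yes/no condition for patients recruited through clinic.

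**The concern.** In a sentence that lists baseline values beside other covariates, the natural reading of the former is the earlier value of the outcome being modelled. The self-management, knowledge, adherence and quality-of-life surveys all have one. The primary outcome does not.

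This is not a gap that an analysis plan can close by itself. A plan can choose covariates, but it cannot adjust for a count that the forms never ask for.

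Two things are at stake. First, by choosing a negative binomial model the protocol expects patients to differ in how prone they are to admission. Earlier admission frequency is a direct measure of that tendency, and without it the model leaves the corresponding variation in the error term. Second, with about 75 patients per arm, admission history may differ between arms by chance, and the analysis would have no direct measure with which to correct it. The background section counts a chance imbalance (there in aetiology) among the weaknesses of the pilot, and randomisation here is stratified by aetiology only.

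**Working it through.** **Step 1: is there a baseline count?** The relevant places in the protocol, side by side:

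| Place | Admissions before randomisation? |
|---|---|
| Baseline – all patients (list) | No item |
| Appendix A, items 1 to 21 | No item |
| Schedules, control and intervention | Admissions row ticked only at Month 12 and Month 24/EOS |
| Appendix J | Both windows start at or after randomisation |
| Inclusion criterion 3 | Yes/no for the clinic route, not a count |
| Resource use survey | Described for end of study as 2-week recall of time and money; form not shown |
| Administrative data (MBS/PBS/AR-DRG) | Described for costs over the study period |

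No displayed form captures the count. Collected at baseline in both arms, and usable as covariates: Child Pugh/MELD, Charlson index, comorbidities, aetiology, demographics and survey scores.

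**Step 2: does the stated sample size depend on it?** Inputs from the sample size section: 3 admissions per person-year under usual care, a 20% reduction (2.4 per person-year), median follow-up 18 months, 20% attrition, 80% power, α = 0.05 (two-sided assumed), total 146. With no dispersion stated, the Poisson form is

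n per arm = (1.96 + 0.842)² × (1/4.5 + 1/3.6) / (ln 0.8)² = 7.85 × 0.5 / 0.0498 = 78.8,

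that is 158 in total, or 198 after dividing by 0.8. This does not reproduce 146. With 24 months, 59.1 per arm gives 148 after attrition. The mismatch is a separate matter. What counts here is that none of these calculations contains a term for baseline adjustment, so the missing count leaves 146 unaffected.

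**Step 3: what could the count be worth?** Take 73 per arm, 18 months (expected counts 4.5 and 3.6) and dispersion k:

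SE² = [(1/4.5 + k) + (1/3.6 + k)] / 73; power = Φ(0.2231/SE − 1.96).

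A covariate that explains a share R² of the between-patient variation replaces k by k(1 − R²). It cannot remove the Poisson part. Both k and R² are assumptions.

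| k | R² = 0 | 10% | 25% | 50% |
|---|---|---|---|---|
| 0.25 | 48% | 50% | 53% | 60% |
| 0.5 | 34% | 36% | 40% | 48% |
| 1.0 | 23% | 24% | 27% | 34% |

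Example, k = 0.5: SE = √(1.5/73) = 0.143, power Φ(1.557 − 1.96) = 34%. With R² = 25%, k becomes 0.375, SE = √(1.25/73) = 0.131, power 40%.

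**Step 4: simulation.** Log-normal patient rates, a 12-month prior count at 3 per year, negative binomial regression without and with log(prior count + 0.5), 600 replicates per setting (Monte Carlo SE about 2 points per power estimate):

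| Correlation of patient rates | k = 0.3 | k = 0.5 | k = 1.0 |
|---|---|---|---|
| 0.7 | 49% to 56% | 38% to 45% | 32% to 36% |
| 0.9 | 48% to 55% | 37% to 49% | 31% to 38% |

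At correlation 0.5 the gain was 1 to 3 points, hardly distinguishable from none. At 0.7 to 0.9 single settings gave 4 to 12 points. Given the Monte Carlo error, roughly 5 to 10 is a fair summary.

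**The case against.** The strongest reply is that the adjustment sentence is permissive and generic. It says that models will allow adjustment, covers several outcomes at once, and does not promise that each is adjusted for its own earlier value. That stands: the sentence is not a broken commitment, and nothing in the protocol relies on it.

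A reader might infer more than the documents support, in four ways:

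- *That baseline adjustment of the primary model is impossible.* It is not. Severity, comorbidity and aetiology are collected in both arms and can enter the model. They may also absorb part of what a prior count would explain, so the gains above, measured against no adjustment, are upper figures.
- *That the count would lift the stated 80% power to about 90%.* This follows from cutting the whole variance by 25%: (1.96 + 0.84)/√0.75 − 1.96 = 1.27, or 90%. It is incoherent. Under the formula above, power at k = 0 is Φ(0.2231/0.0828 − 1.96) = 77%, so 80% is not reached at any k; and at k = 0 there is no between-patient variation to remove. For k of 0.3, 0.5 and 1.0, a 25% cut in total variance needs the covariate to explain 46%, 38% and 31% of the dispersion.
- *That not naming the aetiology strata or a follow-up offset in the model is a fault.* The protocol says "To prevent imbalance in disease aetiology, stratified block randomization will be performed for disease aetiology" and does not exclude aetiology from the model. Such detail commonly belongs in the analysis plan.
- *That the data are lost.* Dated hospital records could supply the count later. The protocol simply does not plan for it.

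It is also fair that prior counts may be sparser than simulated. The rate of 3 per year is the protocol's assumption for follow-up, the look-back would exclude the qualifying admission, and the HCC form (Appendix R) allows for patients only just diagnosed with cirrhosis.

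**Conclusion.** The concern holds in a limited form. As data collection is laid out, the primary outcome has no baseline value, so the adjustment that the protocol allows for all models is not available to the primary model in its most useful form. Randomisation protects the comparison, so this is neither bias nor a type I error problem, and the stated sample size takes no credit for the adjustment.

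The loss is one of precision: roughly 0 to 3 points of power at a patient-rate correlation of 0.5 and roughly 5 to 10 points at 0.7 to 0.9, for k between 0.3 and 1.0. These figures rest on assumed dispersion and correlation, on a prior rate of 3 per year and on no other covariates in the model; sparse histories or existing covariates would shrink them. It is worth correcting because it is cheap, not because the analysis fails without it.

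**What to change.** 1. Add one item to Appendix A for all patients in both arms: the number of unplanned liver-related admissions in a fixed look-back before randomisation (for example 12 months), excluding the admission that qualified the patient. Take it from the records already reviewed for eligibility. For patients already enrolled, complete it from dated hospital records by the same rule in both arms, preferably by someone unaware of allocation.

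2. Add a sentence to the Statistical methods section that the primary negative binomial model includes this count as a baseline covariate. Its functional form and the remaining covariates can be left to the analysis plan.

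3. Clarify the note in Appendix J, "If currently in hospital this counts as an admission in the time period being considered". For patients randomised as inpatients it could be read as placing the qualifying stay in follow-up. The two definitions should agree, so that this stay is handled the same way for everyone.

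The cost is a few minutes per patient and one more model parameter. Admissions to other hospitals may be under-recorded. Since they precede randomisation, that is unrelated to arm provided the same sources are used in both, and would mainly reduce the gain.

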# Trial Management

## Training

To optimize implementation, a two-day training workshop will be held for the four CLD nurses employed by the trial. The workshop will be run by [name], [name] and [name], who developed extensive experience in CLD CDM practice during the pilot. The aims of the workshop will be to familiarize nurses with CLD medical management protocols, standardize nursing approaches to CDM, and research processes and data collection requirements. Data entry will be centralised and double key verification will be included. Consistency checks will be incorporated into the data entry procedure. Principal Investigators from each site will also join for a morning of training about the study requirements, medical protocols and data collection requirements.

All investigators will teleconference initially monthly to oversee quality management and timeline issues related to the project. In addition, a Project Management Executive involved in the day-to-day management ([name], [name], [name] and CLD nurses at SCGH, QEH, LMH, and RAH) will initially teleconference weekly for the first two months, then fortnightly-monthly throughout the duration of the project. The trial managers ([name]) will be responsible for operational management of the trial and [name] will be responsible for data entry and randomisation and will remain separate from day-to-day management.

## Data Monitoring

Outcome data for all endpoints will be monitored at 3-monthly intervals during the trial by the project team and at the trial midpoint to review adverse events, progress and preliminary outcome data.

Data will be submitted by scanning data collection records to the trial data manager. If a patient consents to receiving study surveys electronically, the CLD nurse involved in their care will send fillable surveys at each time point to the provided email address. The surveys will have the patient’s unique study ID allocated. Completed surveys will be emailed back to the CLD nurse, who will then check to ensure there is no identifying information recorded, before forwarding data on to the trial data manager as per standard process. All data will be saved in a secure password-protected computer for the duration of the study, which can only be accessed by the trial data manager.

| Activity Schedule for CONTROL patients | Baseline | Treatment Period  Day 7 to Week 11 are scheduled from the discharge date from hospital.  From Month 3 visits are scheduled from randomisation.  All visits/contacts have a window of +/- 2 days | | | | | | | | | | | | | | | | |
| --- | --- | --- | --- | --- | --- | --- | --- | --- | --- | --- | --- | --- | --- | --- | --- | --- | --- | --- |
|  | Baseline | Day 7 | Day 14 | Week  3 | Week  4 | Week  5 | Week  6 | Week  7 | Week  8 | Week  9 | Week  10 | Week  11 | Month  3 | Month  6 | Month  9 | Month  **12** | Month  18 | Month 24/EOS |
| Informed Consent | X |  |  |  |  |  |  |  |  |  |  |  |  |  |  |  |  |  |
| Child Pugh / MELD | X |  |  |  |  |  |  |  |  |  |  |  |  |  |  |  |  | X |
| SURVEYS (5) | X |  |  |  |  |  |  |  |  |  |  |  | X | X |  | X | X | X |
| Concomitant Medications | X |  |  |  |  |  |  |  |  |  |  |  |  |  |  |  |  | X |
| Comorbidities | X |  |  |  |  |  |  |  |  |  |  |  |  |  |  |  |  | X |
| Charlson Comorbidity Index | X |  |  |  |  |  |  |  |  |  |  |  |  |  |  |  |  |  |
| Randomisation | X |  |  |  |  |  |  |  |  |  |  |  |  |  |  |  |  |  |
| Cost/Resource use survey | X |  |  |  |  |  |  |  |  |  |  |  |  |  |  |  |  | X |
| Admissions to hospital |  |  |  |  |  |  |  |  |  |  |  |  |  |  |  | X |  | X |
| Liver-related appointments |  |  |  |  |  |  |  |  |  |  |  |  |  |  |  | X |  | X |
| Patient Satisfaction |  |  |  |  |  |  |  |  |  |  |  |  |  |  |  |  |  | X |
| Alcohol Use assessment |  |  |  |  |  |  |  |  |  |  |  |  |  |  |  |  |  | X |
| Ascites & HE assessment |  |  |  |  |  |  |  |  |  |  |  |  |  |  |  |  |  | X |
| HCC assessment |  |  |  |  |  |  |  |  |  |  |  |  |  |  |  |  |  | X |
| Osteoporosis assessment |  |  |  |  |  |  |  |  |  |  |  |  |  |  |  |  |  | X |
| Variceal assessment |  |  |  |  |  |  |  |  |  |  |  |  |  |  |  |  |  | X |
| Nutrition assessment |  |  |  |  |  |  |  |  |  |  |  |  |  |  |  |  |  | X |
| End of study outcome |  |  |  |  |  |  |  |  |  |  |  |  |  |  |  |  |  | X |
| Interview for selected pts |  |  |  |  |  |  |  |  |  |  |  |  |  |  |  |  |  | X |

| Activity Schedule for INTERVENTION patients |  | Treatment Period  Day 7 to Week 11 are scheduled from the discharge date from hospital.  From Month 3 visits are scheduled from randomisation. | | | | | | | | | | | | | | | |
| --- | --- | --- | --- | --- | --- | --- | --- | --- | --- | --- | --- | --- | --- | --- | --- | --- | --- |
|  | Baseline | Day 7 | Day 14 | Week  3 | Week  4 | Week  5 | Week  6 | Week  7 | Week  8 | Week  9 | Week  10 | Week  11 | Month  3 | Month  6 | Month  **12** | Month  18 | Month 24/EOS |
| Informed Consent | X |  |  |  |  |  |  |  |  |  |  |  |  |  |  |  |  |
| Child Pugh / MELD | X |  |  |  |  |  |  |  |  |  |  |  | X | X | X | X | X |
| SURVEYS (5) | X |  |  |  |  |  |  |  |  |  |  |  | X | X | X | X | X |
| Concomitant Medications | X |  |  |  |  |  |  |  |  |  |  |  |  |  |  |  | X |
| Comorbidities list | X |  |  |  |  |  |  |  |  |  |  |  |  |  |  |  | X |
| Charlson Comorbidity Index | X |  |  |  |  |  |  |  |  |  |  |  |  |  |  |  |  |
| Randomisation | X |  |  |  |  |  |  |  |  |  |  |  |  |  |  |  |  |
| Carer and GP assessment | X |  |  |  |  |  |  |  |  |  |  |  |  |  |  |  |  |
| GP communication^a^ | X | X |  |  | X |  |  |  |  |  |  |  |  |  |  |  |  |
| Face to Face Contact | X | X |  |  | X |  |  |  |  |  |  |  | X | X | X | X | X |
| Telephone Contact^b^ |  |  | X | X | X | X | X | X | X | X | X | X |  |  |  |  |  |
| Hepatologist OPD |  |  |  |  |  |  |  |  |  |  |  |  | X | X | X | X | X |
| Care Plan review^c^ | X | X |  |  | X |  |  |  |  |  |  |  | X | X | X | X | X |
| Alcohol Use assessment | X |  |  |  |  |  |  |  |  |  |  |  |  |  |  |  | X |
| Ascites & HE assessment | X |  |  |  |  |  |  |  |  |  |  |  |  |  |  |  | X |
| HCC assessment | X |  |  |  |  |  |  |  |  |  |  |  |  |  |  |  | X |
| Osteoporosis assessment | X |  |  |  |  |  |  |  |  |  |  |  |  |  |  |  | X |
|  |  |  |  |  |  |  |  |  |  |  |  |  |  |  |  |  |  |
| Activity |  | Treatment Period  Day 7 to Week 11 are scheduled from the discharge date from hospital. From Month 3 visits are scheduled from randomisation. | | | | | | | | | | | | | | | |
|  | Baseline | Day 7 | Day 14 | Week  3 | Week  4 | Week  5 | Week  6 | Week  7 | Week  8 | Week  9 | Week  10 | Week  11 | Month  3 | Month  6 | Month  **12** | Month  18 | Month 24/EOS |
| Variceal assessment | X |  |  |  |  |  |  |  |  |  |  |  |  |  |  |  | X |
| Nutrition assessment | X |  |  |  |  |  |  |  |  |  |  |  |  |  |  |  | X |
| Admissions to hospital |  |  |  |  |  |  |  |  |  |  |  |  |  |  | X |  | X |
| Liver-related appointments |  |  |  |  |  |  |  |  |  |  |  |  |  |  | X |  | X |
| Cost/Resource use survey | X |  |  |  |  |  |  |  |  |  |  |  |  |  |  |  | X |
| Patient Satisfaction |  |  |  |  |  |  |  |  |  |  |  |  |  |  |  |  | X |
| End of study outcome |  |  |  |  |  |  |  |  |  |  |  |  |  |  |  |  | X |
| Interview for selected pts |  |  |  |  |  |  |  |  |  |  |  |  |  |  |  |  | X |

a. GP Contact is to occur post discharge from any hospitalisation, post home visit, or any major change in the care plan. Please record all contact on the contact log.

b. If the nurse determines that a home assessment is required instead of a phonecall, this is allowed. Please document on the contact log. The contact specified is a minimum requirement. The nurse/Hepatologist can decide for more contacts than designated – please record on the contact log all patient contacts.

c. Care plan reviews include revisiting all care plan actions determined at baseline and ensuring all assessments, screening and surveillance and alcohol counselling are being actioned.

